## Abstract

**Background:**

Preterm and term small for gestational age (SGA) babies are at high risk of experiencing malnutrition and impaired neurodevelopment. Standalone interventions have modest and sometimes inconsistent effects on growth and neurodevelopment in these babies. For greater impact, intervention may be needed in multiple domains—health, nutrition, and psychosocial care and support. Therefore, the combined effects of an integrated intervention package for preterm and term SGA on growth and neurodevelopment are worth investigating.

**Methods:**

An individually randomized controlled trial is being conducted in urban and peri-urban low to middle-socioeconomic neighborhoods in South Delhi, India. Infants are randomized (1:1) into two strata of 1300 preterm and 1300 term SGA infants each to receive the intervention package or routine care. Infants will be followed until 12 months of age. Outcome data will be collected by an independent outcome ascertainment team at infant ages 1, 3, 6, 9, and 12 months and at 2, 6, and 12 months after delivery for mothers.

**Discussion:**

The findings of this study will indicate whether providing an intervention that addresses factors known to limit growth and neurodevelopment can offer substantial benefits to preterm or term SGA infants. The results from this study will increase our understanding of growth and development and guide the design of public health programs in low- and middle-income settings for vulnerable infants.

**Trial registration:**

The trial has been registered prospectively in Clinical Trial Registry – India # CTRI/2021/11/037881, Registered on 08 November 2021.

**Supplementary Information:**

The online version contains supplementary material available at 10.1186/s13063-024-07942-z.

## Introduction

### Background and rationale {6a}

Preterm births (born before 37 completed weeks of gestation) and babies being term small for gestational age (term SGA—birth weight for gestational age below the 10th percentile) present significant global health problems [1, 2]. It is estimated that globally, 11.9 million live births (8.8% of all live births) are preterm, while approximately 21.9 million (16.3%) neonates are born term SGA [3]. The proportion of babies born preterm and term SGA is higher in South Asia compared to other parts of the world [1, 2, 4], and within South Asia, India has the highest proportion of preterm (13.6%) and term SGA (36.5%) babies [1, 2]. These babies comprise 40% of all live births and 65–70% of infants with underweight, stunting, and wasting in Delhi, India [5].

Babies born preterm and term-SGA are vulnerable to serious infections and feeding difficulties [6]. This contributes to an increased risk of death, growth impairment, and neurodevelopmental disorders in early and later life [7, 8]. Evidence from low- and middle-income countries (LMICs) indicates that preterm and term SGA babies have 2–3 times increased risk of being underweight at age 12 to 60 months compared to term appropriate for gestational age (AGA) babies [9]. A similar magnitude of risk was also observed for stunting and wasting [9]. Evidence from systematic reviews suggest that children born as term SGA babies have 0.3 to 0.5 SD lower neurodevelopment scores between 1 and 12 years of age compared to those born term AGA [8, 10, 11]. Preterm and term SGA babies are also at increased risk of neurodevelopment impairment. Preterm babies have lower cognitive and fine motor skills scores (SMD: − 0.70; 95% CI: − 0.73 to − 0.66) and an increased risk of behavioral problems at school age compared to term babies. Additionally, preterm babies have a higher likelihood of motor skill impairment with 40% experiencing mild impairment and 20% experiencing moderate impairment [12, 13]. Preterm and term SGA babies may additionally exhibit a more difficult and less predictable temperament than term AGAs that can pose a challenge for caregivers to provide appropriate responsive care, possibly aggravating the delayed neurodevelopment [14–17].

The factors influencing growth and neurodevelopment in preterm and term SGA infants are multifactorial. It encompasses a range of factors including infant morbidities, breast feeding practices, maternal and infant nutrition, and maternal psychosocial status. Research indicates that standalone interventions targeting these factors have modest and sometimes inconsistent effects on growth and neurodevelopment [18–29]. Health interventions such as prevention of disease through sanitation, treatment of diarrhea, and immunization were found to increase linear growth among children in developing countries [30–32]. Enteral iron supplementation has been found to improve length among preterm and LBW infants [MD 0.69 cm, 95% CI 0.01 to 1.37] in the first 6 months of life [33, 34], and kangaroo mother care (KMC), which includes exclusive breastfeeding, has been shown to improve weight [4.08 g/day (2.30 to 5.86)] and length [0.21 cm/week, (0.03 to 0.38)] in low birth weight infants [21, 34, 35]. Early child stimulation activities among preterm infants have been found to improve cognitive (developmental quotient (DQ): SMD: 0.32 SD; 95% CI: 0.16 to 0.47) and motor outcomes in infancy (motor scale DQ: SMD 0.10 SD, 95% CI: 0.01 to 0.19) [27]. For greater impact, intervention may be needed in several domains, i.e., health, nutrition, and psychosocial care and support, delivered concurrently [36, 37]. Improving the mother’s postnatal health, nutritional status, and psychological well-being may also be critical for implementing interventions promoting optimal growth and neurodevelopment of preterm and term SGA babies [37, 38].

The first 1000 days of life are crucial for subsequent growth and brain development. Insufficient nutrition, repeated infections, and sub-optimal care have negative impacts on both [39, 40]. This is particularly important for preterm and term SGA infants, as achieving postnatal catch-up growth within the first 6 months of life is strongly associated with better neurodevelopment in preschool, school-age, and at later stages [36, 41–44]. Studies have shown that the likelihood of catch-up growth in preterm babies from LMICs is limited [45]. There is very limited evidence regarding catch-up growth in term SGA infants in LMICs.

Identification of an intervention package that substantially improves the growth and neurodevelopment of preterm and SGA infants may hold the potential to reduce undernutrition in infancy and may contribute to improved health, educational achievement, and economic status in adulthood for a substantial proportion of the Indian population [46]. This package should include intervention that have been documented to have at least modest effects when delivered on their own and are expected to achieve synergistic effects on growth and neurodevelopment when combined. We are conducting an individually randomized controlled trial in low to middle socioeconomic neighborhoods of Delhi to ascertain the efficacy on growth and neurodevelopment of an integrated package of health, nutrition, and early child stimulation and responsive care intervention delivered concurrently to term SGA and preterm infants and their mothers. The comparator group in this study are infants who are receiving routine care from either government or private hospitals. This comparison is crucial to determine whether the intervention provides any additional benefits over and above the current standard of care.

### Objectives {7}

The primary objectives are to estimate the efficacy of concurrent delivery of a health, nutrition, and early child stimulation and responsive care intervention package during the first year of life on attained weight and weight for age *z* score (WAZ) at 12 months of age for (i) preterm infants and their mothers and (ii) term SGA infants and their mothers.

The secondary objectives are to determine the effects of the same package on mortality, morbidity, nutritional status, and neurodevelopment in infants and nutritional status and depressive symptoms among mothers in the first year of infant age. We will also estimate the effect on household consumption and expenditures at 6 and 12 months of infant age.

### Trial design {8}

An individually randomized controlled trial with parallel design (1:1), stratified by preterm and term small for gestational age (SGA). The trial hypothesis is that the integrated and concurrent delivery of interventions in the domain of health, nutrition, and early child stimulation and responsive care to preterm or term SGA infants and their mothers during infancy will increase their mean attained weight and weight-for-age *z* scores by at least 0.2SD or more at 12 months of age. Blinding will be implemented at the outcome assessor and data analyst level to minimize bias. All design elements of the trial have been carefully considered to ensure the validity and reliability of the trial results.

## Methods: participants, interventions, and outcomes

### Study setting **{9}**

The study is an individually randomized trial and is being conducted in urban and peri-urban low to middle socioeconomic neighborhoods of South Delhi, India [47]. In this setting, the proportions of infants born preterm (~ 15%) and SGA (~37%) are similar to the national average [5]. The prevalence of stunting and underweight at 12 months of age in preterm infants is 31% and 20% and in term SGA 34% and 36%, respectively [48]. Approximately 45% of women have secondary level or higher education. Almost all (95%) births are institutional, with 80% taking place in public health facilities. Four fifths (around 80%) of mothers return home within 72 h of delivery.

### Eligibility criteria **{10}**

#### Inclusion criteria

Preterm or term SGA infants and their mothers with ultrasound dating scan done within 20 weeks of gestation are eligible for participation.

#### Exclusion criteria

Infants with congenital malformations (affecting feeding or the ability to take measurements), mothers intending to leave the study area within the next 12 months, or babies or mothers who are hospitalized for more than 14 days post-delivery are excluded from the study.

### Sample size {14}

There are two strata: preterm and term SGA. Sample sizes are calculated for 90% power and 95% confidence for each stratum. Assuming a minimum of 0.20 SD mean difference in weight (which translates to a 200 g weight difference) or WAZ scores between the intervention and control arms at 12 months, a total of 1054 infants per strata, i.e., (527 infants per arm per strata) are required [5].

### Recruitment {15}

Accounting for a possible 20% loss to follow-up from enrolment to 12 months of age, we will need 650 infants per arm per stratum. We will therefore enroll a total of 2600 infants (1300 preterm and 1300 term SGA).

With 650 infants in each stratum in each arm, assuming a prevalence of underweight of 25% in the control arm at 12 months of age, we will be able to detect a 30% relative reduction in underweight, with 90% power and 95% confidence level. A narrow effect size in the hypothesis has been considered to adjust for some earlier impact of similar intervention in the study area, by our team [1]. We will also be able to detect a difference of 3 composite standard score–points (0.2 SD) in the domains of the Bayley Scales of Infant and Toddler Development, 3rd Edition (BSID-III).

Assuming 25% of babies are term SGA and 15% preterm, and 40% attrition from pregnancy identification to enrolment, we will probably need gestational age assessment through dating ultrasounds in ~13,000 pregnancies [1]. The sample size estimation for this study was conducted using *power* commands in STATA.

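### The 90% power stated for a 30% reduction in underweight counts all 650 enrolled infants per arm; after the protocol's own 20% loss it is about 84%, and on its stratum-specific setting prevalences about 73% (preterm) and 97% (term SGA)

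*Protocol article*

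**What the plan says.** The protocol article sizes the two strata separately: "Sample sizes are calculated for 90% power and 95% confidence for each stratum" (Sample size). For the primary outcome, a 0.20 SD difference in weight or WAZ, it arrives at 527 infants per arm per stratum. The Recruitment section then raises that number: "Accounting for a possible 20% loss to follow-up from enrolment to 12 months of age, we will need 650 infants per arm per stratum".

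The next paragraph of the same section turns to underweight at 12 months. It opens "With 650 infants in each stratum in each arm, assuming a prevalence of underweight of 25% in the control arm at 12 months" and concludes "we will be able to detect a 30% relative reduction in underweight, with 90% power and 95% confidence level". One prevalence and one power figure serve both strata.

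The Study setting section reports stunting and underweight at 12 months in this population, in that order: "in preterm infants is 31% and 20% and in term SGA 34% and 36%, respectively". Underweight is therefore 20% in preterm and 36% in term SGA infants. The article gives no reason for using 25% in both.

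Underweight is listed among the key secondary outcomes (Outcome measures) and is defined as WAZ below −2 SD (Definitions).

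**The concern.** Two inputs to the underweight statement sit badly with the rest of the article.

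- **The number analysed.** The loss allowance is applied to the primary outcome and then left out for an outcome computed from the same 12-month weight. An infant without that weight contributes to neither.
- **The control prevalence.** A single value is used for two strata that are sized and analysed separately and whose setting prevalences, as reported in the article itself, are 16 percentage points apart (36% − 20%).

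The first lowers power in both strata. The second overstates power in the preterm stratum and understates it in term SGA. What is at stake is how a secondary result will be read. The Discussion counts adequate power in each stratum among the trial's strengths, so a null underweight result in preterm infants could be read as coming from a comparison with 90% power when the article's own figures imply less.

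**Working it through.** **Inputs.** Two-sided 5% (my reading of the 95% confidence level; sidedness is not stated), 1:1 allocation, 30% relative reduction (Recruitment). Enrolled 650 per arm per stratum and 20% loss (Recruitment), so evaluable = 650 × 0.8 = 520. Control prevalence 25% (Recruitment), or 20% preterm and 36% term SGA (Study setting).

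**Formula.** With control prevalence p₁, p₂ = 0.7 p₁ and p̄ = (p₁ + p₂)/2,

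power = Φ{ [(p₁ − p₂) − 1.96 √(2p̄(1 − p̄)/n)] / √([p₁(1 − p₁) + p₂(1 − p₂)]/n) }.

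**Step 1: reproduce the stated figure.** p₁ = 0.25, p₂ = 0.175, p̄ = 0.2125, n = 650. The difference is 0.075, the null term is 1.96 × 0.02269 = 0.0445, and the alternative SE is 0.0226. Power = Φ(0.0305/0.0226) = Φ(1.35) = 91.2%. With a continuity correction it is 90.0%, and the continuity-corrected sample size for 90% power is exactly 650 per arm (624 without correction). The stated 90% is therefore reproduced with all 650 counted as observed at 12 months.

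**Step 2: apply the protocol's own loss, keep 25%.** n = 520: null term 1.96 × 0.02537 = 0.0497, alternative SE 0.02526. Power = Φ(0.0253/0.02526) = Φ(1.00) = about 84% (82% with continuity correction).

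**Step 3: use the setting prevalences.**

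| Control prevalence | 30% reduction gives | Power, n = 650 | Power, n = 520 | Evaluable per arm for 90% power | Relative reduction detectable at 90% power, n = 520 |
|---|---|---|---|---|---|
| 25% (as assumed) | 17.5% | 91% | 84% | 624 | about 33% |
| 20% (preterm) | 14% | 82% | 73% | 822 | about 37% |
| 36% (term SGA) | 25.2% | 99% | 97% | 381 | about 26% |

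For preterm at n = 520: difference 0.06, null term 0.0457, alternative SE 0.0232, power = Φ(0.62) = 73%.

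**Step 4: sensitivity to method.** Preterm power at 520 is 70% with continuity correction and 72% with a Wald test on the log relative risk. One-sided at 5% it would be 82%, still below 90%. Using 527 instead of 520 gives 74%.

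**Step 5: primary outcome.** A 0.2 SD difference with 520 per arm has Φ(0.2 √(520/2) − 1.96) = Φ(1.265) = 89.7% power, so the sizing of the trial itself is essentially unaffected.

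**The case against.** *The 25% is a declared assumption.* This stands. The setting figures come from a cited source and are not this trial's control arm, so they do not show that 25% is false. A reader might infer that neither stratum can have 25%; the article supports only that 25% matches neither reported figure and is unexplained. The loss-to-follow-up point does not depend on this, since it holds at 25%.

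*The 20% loss is only an allowance.* Also fair. At a 20% prevalence, preterm power runs from 73% with the full loss, through 78% with 10% loss (585 per arm), to 82% with none. The 73% is the lower end of that range, but it rests on the same allowance that the protocol used to set enrolment.

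*Secondary outcomes may be imputed.* The Main effects section allows this, but it declines to impute the 12-month primary outcome because missingness at random is doubtful. Underweight is derived from that same WAZ, and imputation would not restore the information of 650 observed infants.

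*Is the 30% reduction at odds with the 0.2 SD hypothesis?* A reader might infer so, because a uniform 0.2 SD shift in a normal WAZ distribution would reduce underweight by less than 30%. The documents do not support that criticism. The trial hypothesis and the sample size section both make 0.2 SD a minimum. Under a normal model with unchanged SD, a 30% reduction needs a shift of only 0.24 SD (20% control), 0.26 SD (25%) or 0.31 SD (36%), all compatible with that minimum. A uniform shift is also not what the plan presumes: it compares percentiles by quantile regression and gives extra food supplement to older infants with growth failure, so the lower tail may move more than the mean.

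**Conclusion.** The power statement for underweight is wrong as written. On its own prevalence, about 84% should replace 90% once the protocol's loss allowance is applied. On the setting prevalences, the two strata differ: about 73% in preterm and about 97% in term SGA. The preterm figure should not be quoted alone, because the same two changes raise power in term SGA above the stated level.

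These values assume a two-sided 5% test of two proportions, the full 20% loss in both arms, and, for the stratum figures, that control-arm prevalence resembles the setting figures. It would go too far to say that the trial is underpowered overall. Underweight is one of several key secondary outcomes, and no analysis, estimand or enrolment target depends on this sentence. It should be fixed, but it is not critical.

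**What to change.** Replace the underweight sentence in the Recruitment section with one of these:

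1. Power by stratum on 520 evaluable infants per arm, using the Study setting prevalences: 90% power for a relative reduction of about 37% in preterm (20% control) and about 26% in term SGA (36% control). Equivalently, about 73% and 97% power for a 30% reduction.
2. If 25% is kept for both strata, give its justification and state about 84% power for a 30% reduction with 520 per arm (90% power for about 33%).

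Either way, say explicitly that the number is evaluable infants at 12 months. The cost is rewording one sentence and its figures; enrolment, design and analysis stay as they are. Under option 1 the preterm figure becomes less favourable and the term SGA figure more so.

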### Intervention description {11a}

The intervention has three domains—health, nutrition, and early child stimulation-and-responsive care—and is being delivered from birth until 12 months of age. These were selected based on their impact on growth and developmental outcomes in preterm, term SGA, and LBW infants (Table 1). The details of this intervention are listed in Additional file 1.

**Table 1 Tab1:** Summary of the intervention

Component	Intervention	Control
**Infants**		Care routinely sought from usual sources -government (free of cost) and private providers
Health	Illness ascertainment through reports by caregivers and by team, at home visits Facilitation of medical care-seeking/access Provision of zinc and ORS for the management of diarrhea Counselling on immunization and handwashing practices	
Nutrition	*0 to 6 months* Growth monitoring based on WHO standard growth charts. Assessment by physician, lactation counsellor, and psychologist (for mothers) if there is growth failure Management of severe acute malnutrition (SAM) Counselling and support for exclusive breastfeeding Expressed breastmilk feeding, if indicated Kangaroo mother care during the neonatal period Lactational counselling and additional breastfeeding support for breastfeeding problems Micronutrient supplementation of iron, vitamin D, zinc, or other B vitamins *7 to 12 months* Counselling on continued breastfeeding, complementary feeding, responsive feeding, food hygiene, and immunization Iron and folic acid supplementation	
Early child development	Counselling and demonstration of early child play and responsive care for the infant	
**Mother**		
Health	Counselling on postnatal check-ups and family planning	
Nutrition	*6 months postpartum* Nutritional supplementation to mother in the form of healthy snacks, calcium and vitamin D, iron and folic acid supplementation, and multiple micronutrient tablets	
Psychosocial support	Promotion of positive thinking and problem-solving skills	

In the health domain, the key components are prevention, early identification, and management of infections [49]. Mothers are counselled to seek vaccination of the infants according to the national immunization schedules. They are also counselled and given demonstrations on correct handwashing practices during food preparation and feeding of the baby. Any illnesses reported by caregivers are managed at the study clinic in the collaborating hospital or any nearby health facilities [50, 51].

From enrollment to 6 months, mothers are counselled and supported to breastfeed their infants exclusively. For late preterm infants (34 to 37 weeks) who show signs of tiring quickly and suckle for less than 5 min, the mother is encouraged to give expressed breast milk feeding after each breastfeed. For infants less than 34 weeks gestation, expressed breastmilk is given following each direct feed. Mothers are taught to express, store and feed breastmilk [52, 53].

Mothers are taught to keep the baby in the skin-to-skin contact (SSC) position, i.e., upright between her breasts, and counselled to give SSC as long as possible during the day and night, in a semi-reclining or supine position, till the baby is 28 days old or wriggles out.

All infants are provided micronutrient supplementation daily as per 2022 WHO guidelines for preterm or LBW infants (iron 2–4 mg/kg/day, vitamin D 800 IU/day, and zinc 2–3 mg/kg/day) [54].

Caregivers of infants aged 6 to 12 months are counselled on timely introduction of complementary foods at 6 months, on the frequency of feeding and types of food to be fed and their amounts, and recipes for energy and nutrient-dense meals made from locally available and culturally acceptable foods are shared. A daily milk cereal mix packet (125 Kcal per day, and 5 g protein including 80% to 100% recommended daily allowances (RDA) of micronutrients) is provided to all infants (see Additional file 2 for detailed composition). The nutritional supplement provides around 50 to 60% of the daily energy requirement between 6 to 12 months of age, assuming the infant is breastfed [55]. Mothers are counselled and supported to continue breastfeeding till at least 12 months of age.

Growth is monitored fortnightly in the first 2 months of life and subsequently monthly to identify growth failure. Growth failure is defined using both attained growth and growth velocity. Attained growth is calculated based on WAZ and LAZ in the first 6 months and WLZ and LAZ in the next 6 months using WHO growth standards. Growth velocity is monitored based on WHO weight velocity standards [56]. Weight velocity below the 15th centile for term SGA and below the 25th centile for preterm infants is defined as growth failure [5]. Attained growth and growth velocity of infants in the intervention arm are monitored using an electronic monitoring system, which calculates growth indices (attained and velocity *z* scores) in real-time.

Infants with growth failure are referred to the study clinic and assessed for morbidity, breastfeeding, and complementary feeding practices. In addition to support on how to manage the morbidity of their infants, mothers of infants under 6 months with growth failure are provided with additional counselling on the importance of exclusive breastfeeding. Infants older than 6 months with growth failure are given one packet of additional food supplement (125 Kcal, ~ 5 g protein) per day, in addition to breastfeeding support.

The intervention for early child development (ECD) have been adapted from the “Care for Child Development” manual developed by WHO and UNICEF [57]. The strategies involve fostering a strong connection between the research team and the mother or primary caregiver, aiming to boost her motivation for better childcare. It includes observing the mother’s play and interaction with the child and providing recommendations for and demonstrations of age-appropriate activities for her to engage with her child. Additionally, assistance is being provided to the mother during the activities, while encouraging her to practice them independently. The developmental screening tool, Ages and Stages Questionnaire version III (ASQ-3) will be administered at 4, 6, 9, and 11 months of infant age to identify early delays in child development [58]. Infants whose parents have concerns about developmental delay and those with ASQ-3 scores below the age-specific cut-off are assessed by the study psychologist and referred to a developmental pediatrician if needed.

Mothers receive counselling on postnatal check-ups and family planning practices. Contraceptives are provided if requested. Mothers are provided with ~1 RDA of daily multiple micronutrient supplements (Additional file 3 for the detailed composition of the micronutrient supplement, Riconia Silver) and locally prepared snacks that align with the Indian Council of Medical Research (ICMR) guidelines for 6 months post-partum [59]. The daily snacks provide 600 kcal with 25–30% of energy (150–180 kcal) from fats and 13% of energy from proteins (80 kcal). It contains 20 g of protein from a mix of plant- and animal sources, with ∼30% (5.4–6 g) of the protein coming from a dairy source.

All mothers are also counselled for their psychological well-being using a module adapted from the WHO Thinking Healthy Manual [60]. The intent is to promote psychological well-being and strengthen the mother’s problem-solving skills. The adapted version of the module emphasizes five basic principles—empathetic listening, guided discovery using pictures, family engagement, problem-solving, and behavioral activation—and is aligned to the local context in order to make it easier for the mothers to comprehend and practice. Patient Health Questionnaire 2-item (PHQ-2) along with the assessment of suicidal ideation are being used to screen for postpartum depression. Mothers suspected of having depression are referred to a clinical psychologist for further evaluation.

